#### Exclusion criteria

Patients are to be excluded if they have brain metastasis, high risk of fracture due to bone metastasis, severe emotional instability, cardiorespiratory compromise or uncontrolled infection; relapse or progression of blood cancer; alterations in communication or significant cognitive impairment that might hinder data collection; bronchiectasis or lung disease other than COPD; other comorbidities that might hinder or prevent them from following the exercise programme; or uncontrolled high blood pressure (systolic > 200 or diastolic > 110 mmHg).

### Recruitment

The Oncology, Haematology and Pulmonology services, primary care doctors and the Mental Health Network of Bizkaia have established an active surveillance system to identify patients with the chronic conditions under study. Doctors will inform patients about the study and invite them to participate. After signing an informed consent form, patients will be referred by the study coordination group to their primary care doctor who will gather baseline data. Before each patient’s group allocation is known, a fitness and health professional will measure the study variables at baseline and provide the standardised healthy lifestyle prescription, encouraging physical activity, a balanced diet and smoking cessation.

### Randomisation

Once informed consent has been obtained and baseline measurements have been taken, patients will be randomised blindly and centrally to either the EG or PVS group, stratified by illness type, at the coordinating centre, the Primary care Research Unit of Bizkaia of the Biocruces Bizkaia Health Research Institute. The randomization will be performed using computer-generated random numbers in a 1:1 ratio, stratified by illness type, with a block size of 4 or 6. (Fig. 1).

**Fig. 1 Fig1:**
[figure not shown]
Schematic overview of the process for programme implementation and evaluation

### Protocol for the PVS group

On recruitment, all participants will receive a standard healthy lifestyle prescription, encouraging physical activity, a balanced diet and smoking cessation, using the PVS computer tool, which is integrated into the electronic health record. In addition to other measurements at 3, 6 and 12 months, the follow-up will include assessment of potential changes in these habits.

### Protocol for the EfiKroniK group

First phase: the EfiKroniK group are to participate in an innovative physical exercise programme supervised by fitness and health professionals, ensuring patient safety and adjusting the intensity of the exercise to each patient. In this phase, patients are to develop the skills necessary to become an expert regarding the ideal dose of exercise for them. It consists of 36 sessions of exercise of progressively increasing intensity and tailored to the physical condition of each patient, assessed based on metabolic thresholds. Two sessions a week are to be performed in the laboratory, combining aerobic and strength exercises with stretching, under the supervision of fitness and health professionals and one session a week independently near the health centre, monitored with an HR monitor programmed by the fitness and health professionals. In addition to HR measured with the monitor, exercise is monitored with the modified Borg Rating of Perceived Exertion Scale [35] and the appearance of any symptoms.

Second phase: In this phase, patients are to work independently following a physical exercise programme similar to that of the first phase, taking advantage of resources in the community. To make this feasible, patients are to have been trained during the first phase in the type of exercise and appropriate intensity (Borg Scale, HR monitor, symptoms), and at the end of the 3-month training programme, we will contact individuals who can provide support in the community.

We will calculate the real dose of physical exercise each person has been exposed to: cumulative metabolic equivalent (MET)*h/week and time spent doing moderate and/or vigorous intensity of exercise and intensity of exercise under supervision based on the percentage of heart rate reserve (HRR).

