#### Intensity of aerobic exercise

The American College of Sports Medicine recommends doing at least 150 min/week of moderate or 75 min/week of vigorous physical activity or a combination of both [36]. Regarding the definition of relative intensity, 45–59% of the HRR corresponds to a moderate intensity. Use of this indicator, however, implies carrying out a maximum stress test, the results of which may be distorted by the high degree of fatigue, weakened immune system and reduced peripheral muscle strength of patients who are receiving intensive treatments and have a low level of fitness [28]. Furthermore, at the same relative intensity (59% of HRR), the metabolic response varies greatly between individuals [21]. For these reasons, we will measure metabolic thresholds in each patient to allow us to: 1) assess patient aerobic capacity and changes therein, given their strong association with maximum rate of oxygen consumption (VO2max), 2) ensure patient safety and provide them with a level of metabolic stimulus that is similar across patients and effective in improving biochemical parameters (e.g., reduction in inflammation and improvements in the immune system, blood glucose levels and lipid profile), and 3) obtain a reference for designing exercise intensity zones for each patient, in terms of speed and HR as well as perceived exertion. In particular, the first lactate threshold (LT1) can be used in this way given the parallel response between the exponential increase in lactate concentrations that occurs after this threshold and the secretion of catecholamines, neurotrophic hormones associated with improvements in cognitive function (BDNF) and anti-inflammatory interleukins (IL-6) involved in reductions in tumour size and reproducibility [37].

The speed at the LT1 determined during an incremental lactate test and the corresponding HR will define the lower limit of the moderate-intensity zone. On the other hand, the speed at the anaerobic threshold, used as a measure of the maximal lactate steady state (MLSS) [36], and the corresponding HR will be taken as the upper limit of the moderate-intensity zone.

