Based on the individual metabolic thresholds, we will design five intensity zones. The zone of low-intensity training (LIT) corresponds to exercise carried out at an HR lower than that at LT1 (~ 20% of the HRR) and the zone of moderate intensity to exercise carried out between LT1 and the MLSS (~ 20–85% of HRR or between 1 and 2.3 Mmol/L), this in turn being divided into three equally-sized zones: low-moderate (M1), medium-moderate (M2) and high-moderate (M3) intensity. Finally, the zone of high-intensity training (HIT) (>MLSS, > ~ 85% of the HRR).

During the first month, participants will start carrying out sessions involving endurance exercise, which will be divided into 3 intervals of 8 min each at an M2 intensity, alternating with 2 min at an M1 intensity. In the session in which patients work independently, they will be monitored with HR monitor and it will be explained that they should exercise for 30 min and for as much of that time as possible at M1.

During the second month, the maximum intensity of the intervals will increase to M3, nearing the anaerobic threshold HR. Specifically, the fully supervised exercise will be divided into four intervals of 5 min at M3, alternating with 3 min at M1, while the indirectly monitored (semi-supervised) session will be of 30 min at M2 (Fig. 2).

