### Outcome measures

These measurements are made by an interviewer blind to group allocation.

*Primary outcome measure* (baseline, 3, 6 and 12 months):
Cardiorespiratory functional capacity, as assessed using a 400-m walk testChanges in health-related quality of life, as assessed using the 36-item Short-Form Health Survey (SF-36) and disease-specific questionnaires: the European Organization for the Research and Treatment of Cancer Quality of Life Questionnaire (EORTC QLQ-C30) in patients with cancer; and the COPD Assessment Test (CAT) and Chronic Respiratory Disease Questionnaire (CRQ) in patients with COPD.

*Secondary outcome measures* (baseline, 3, 6 and 12 months):
Muscle strength test measured by the handgrip strength and sit-and-stand testsThresholds for lactate (LT1 and MLSS), HR, and accelerometer activity counts for tailoring the exercises, determined in submaximal walking or running tests. For detecting LT1, a test will be carried out on a 20-m track. This will be an incremental test combining 2-min active period and 1-min rest period. To help the participant adjust their speed in each 2-min period, red markers will be placed every 5 m on the floor and the wall on both sides and two large cones on the floor at each end of the track. Participants will be asked to reach the next red markers each time they hear a beep, continually adjusting their speed but without stopping; that is, they should go faster or more slowly seeking to pass each set of markers at the time of the corresponding beep. The speed will start at 2.4 km/h in the first stage; and will increase by 0.61 km/h each stage [40]. At the end of each stage, the following will be recorded: HR, Rating of Perceived Exertion and lactate concentration, by taking a blood sample from each earlobe to find the minimum lactate equivalent (LEmin) above which the lactate concentration starts to increase exponentially. Hence, the aerobic threshold is defined as the intensity of exercise (speed) at which the lowest recorded lactate level is followed by changes ≥0.1 mmol/L in the next stage and > 0.2 mmol/L the one after [25]. The test will be stopped if the participant becomes exhausted or lactate levels exceed 3 mmol/L.

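### The supervised-intensity part of the exercise dose is expressed as a percentage of heart rate reserve, a measure the protocol itself sets aside, although individual lactate-derived heart-rate zones are already planned

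*Protocol article*

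**What the plan says.** The protocol article, under Protocol for the EfiKroniK group, says that the real exercise dose will be calculated for each person. The components are "cumulative metabolic equivalent (MET)*h/week and time spent doing moderate and/or vigorous intensity of exercise" and, for the supervised part, "intensity of exercise under supervision based on the percentage of heart rate reserve (HRR". The same section plans heart-rate monitoring of exercise.

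The section Intensity of aerobic exercise takes up heart rate reserve (HRR) as an indicator of relative intensity and raises two objections. The first: "Use of this indicator, however, implies carrying out a maximum stress test, the results of which may be distorted by the high degree of fatigue", together with weakened immunity and muscle strength in patients who are on intensive treatment and unfit. The second: "at the same relative intensity (59% of HRR), the metabolic response varies greatly between individuals". For these reasons the protocol turns to metabolic thresholds measured in each patient. The moderate zone runs from the first lactate threshold (LT1) to the maximal lactate steady state (MLSS), each with its own heart rate. It continues: "Based on the individual metabolic thresholds, we will design five intensity zones". These are LIT below LT1, three equal moderate zones M1, M2 and M3, and HIT above MLSS.

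Under Outcome measures, the thresholds are "determined in submaximal walking or running tests". The incremental test ends at exhaustion or when lactate exceeds 3 mmol/L. No maximal test is described.

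The dose serves the dose-response objective (Clinical objectives) and the by-protocol analysis (Statistical analysis).

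**The concern.** The protocol explains why a percentage of HRR may mislead in these patients, then uses that percentage to describe how hard they exercised under supervision. There are two separate difficulties.

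- **Measurement.** The percentage needs a maximal heart rate, and none is measured in the tests described. If the value is estimated, the error sits in the denominator and is the same for all of a patient's sessions, so averaging over sessions does not remove it.
- **Meaning.** Even with a perfectly known maximal heart rate, the protocol says that equal percentages do not imply equal metabolic stimulus. Two patients with the same recorded intensity may have received different doses in the sense the trial cares about.

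The Discussion presents the minimum therapeutic dose as a main contribution of the study. Error in an exposure generally tends to flatten an estimated dose-response slope. The protocol links the distortion to intensive treatment and low fitness. If these differ between the four illnesses, the error could also differ between them and blur the planned analysis of illness as a moderator.

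**Working it through.** There is no stated figure to reproduce. The check compares the sections and adds some supporting arithmetic.

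**1. What each scale needs and what the protocol supplies**

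| Scale for supervised intensity | Needs | Supplied in the protocol |
|---|---|---|
| Percentage of HRR | Session, resting and maximal heart rate | Session heart rate from the monitor; no measured maximal heart rate described |
| Individual lactate zones | Session heart rate; heart rate at LT1 and at MLSS | Monitor, incremental lactate test and MLSS test |

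Only the second scale can be built entirely from planned measurements. The protocol already takes this approach elsewhere: under Outcome measures, weekly physical activity is scored against personal activity-count thresholds.

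**2. Approximate position of the zones on the HRR scale**

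The protocol puts LT1 at about 20% and MLSS at about 85% of HRR, with three equal zones between them. Taking the thirds as equal on this scale (an assumption), the width is (85 − 20)/3 = 21.7 points:

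- M1: about 20 to 41.7%
- M2: about 41.7 to 63.3%
- M3: about 63.3 to 85%

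These are general equivalents. They do not provide a patient's own maximal heart rate.

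**3. Sensitivity to the maximal heart rate**

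Formula: %HRR = (session HR − resting HR) / (maximal HR − resting HR). All heart rates below are assumed; the protocol gives none.

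*Example A:* resting 70, session 115.

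| Maximal HR | %HRR | Approximate zone |
|---|---|---|
| 150 | 45/80 = 56% | M2 |
| 160 | 45/90 = 50% | M2 |
| 170 | 45/100 = 45% | M2 |

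*Example B:* resting 75, session 120.

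| Maximal HR | %HRR | Approximate zone |
|---|---|---|
| 130 | 45/55 = 82% | M3 |
| 140 | 45/65 = 69% | M3 |
| 150 | 45/75 = 60% | M2 |
| 160 | 45/85 = 53% | M2 |
| 170 | 45/95 = 47% | M2 |

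In example A, an error of 10 beats either way changes the recorded intensity by 5 or 6 points but not the approximate zone. In example B, the same error around 150 gives 53 to 69% and crosses from M2 to M3. In every row the session stays within about 20 to 85%, so it remains moderate by the trial's own definition. The error affects graded intensity, not whether a session counts as moderate.

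**4. Definition of moderate and vigorous time**

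The dose sentence counts moderate and vigorous time without saying which definition applies. Moderate is defined in the aerobic-intensity section as LT1 to MLSS. None of the five zones is called vigorous.

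**The case against.** The strongest reply is that prescribing and describing are different tasks. The reasons against HRR are given for choosing thresholds to assess capacity, keep patients safe and set zones. They do not forbid a percentage of HRR as a summary of exercise done. It is also only one of three components, and a condensed article may leave the source of the maximal heart rate to a manual.

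Much of this stands. It limits the point to one component of secondary analyses, and the missing source of maximal heart rate would not be a finding by itself. It does not answer the second difficulty: if the same percentage carries very different metabolic responses, the percentage is a weak exposure for a dose-response question, however maximal heart rate is obtained.

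Stronger readings are tempting but not supported:

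- **Two definitions of moderate.** A reader might set "45–59% of the HRR corresponds to a moderate intensity" against the LT1-to-MLSS zone (about 20 to 85%) and infer that counted minutes differ several-fold. The narrower band is a general guideline figure that the protocol sets aside in the next sentence. The trial has one definition, and comparing the widths of the two bands says nothing about minutes in its data.
- **The whole dose rests on HRR.** MET-hours per week and time at moderate or vigorous intensity are listed beside it.
- **HRR is declared unreliable in this trial.** The text says that results may be distorted, and says it of patients on intensive treatment with low fitness, not of every participant.

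**Conclusion.** The point holds in a limited form. The supervised-intensity component of the dose uses a scale that the protocol gives two reasons to avoid, and the tests described do not measure the maximal heart rate it requires. A better exposure variable is available from data already planned.

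The size is modest. One of three dose components is affected, in the dose-response and by-protocol analyses only; the primary intention-to-treat comparison is untouched. Under assumed heart rates, an error of 10 beats in maximal heart rate shifts the percentage by about 5 to 9 points and sometimes moves a session between adjacent moderate zones. The resulting weakening of a dose effect cannot be quantified from the document. The conclusion assumes that no maximal test is done outside what the article describes. If one is, the measurement difficulty eases, but the difference in metabolic response at equal percentages remains. The change is worth making because it is cheap.

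**What to change.** This concerns the analysis variable only and leaves the exercise prescription unchanged.

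1. In the dose-response and by-protocol analyses, express supervised intensity as minutes spent in each patient's own lactate-derived heart-rate zones (LIT, M1, M2, M3, HIT), taken from the heart-rate recordings.
2. State that moderate time in the dose calculation means LT1 to MLSS, as in the section on aerobic intensity, and state which of the five zones counts as vigorous.
3. Keep the percentage of HRR as a descriptive variable only, and say where the maximal heart rate comes from.

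The cost is a few sentences in the analysis text. Heart-rate monitoring and individual zones are already planned, so no new measurement is needed. The small downside is less direct comparability with studies that report percentages of HRR; keeping that figure descriptively largely covers this.

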#### Intensity of aerobic exercise

The American College of Sports Medicine recommends doing at least 150 min/week of moderate or 75 min/week of vigorous physical activity or a combination of both [36]. Regarding the definition of relative intensity, 45–59% of the HRR corresponds to a moderate intensity. Use of this indicator, however, implies carrying out a maximum stress test, the results of which may be distorted by the high degree of fatigue, weakened immune system and reduced peripheral muscle strength of patients who are receiving intensive treatments and have a low level of fitness [28]. Furthermore, at the same relative intensity (59% of HRR), the metabolic response varies greatly between individuals [21]. For these reasons, we will measure metabolic thresholds in each patient to allow us to: 1) assess patient aerobic capacity and changes therein, given their strong association with maximum rate of oxygen consumption (VO2max), 2) ensure patient safety and provide them with a level of metabolic stimulus that is similar across patients and effective in improving biochemical parameters (e.g., reduction in inflammation and improvements in the immune system, blood glucose levels and lipid profile), and 3) obtain a reference for designing exercise intensity zones for each patient, in terms of speed and HR as well as perceived exertion. In particular, the first lactate threshold (LT1) can be used in this way given the parallel response between the exponential increase in lactate concentrations that occurs after this threshold and the secretion of catecholamines, neurotrophic hormones associated with improvements in cognitive function (BDNF) and anti-inflammatory interleukins (IL-6) involved in reductions in tumour size and reproducibility [37].

The speed at the LT1 determined during an incremental lactate test and the corresponding HR will define the lower limit of the moderate-intensity zone. On the other hand, the speed at the anaerobic threshold, used as a measure of the maximal lactate steady state (MLSS) [36], and the corresponding HR will be taken as the upper limit of the moderate-intensity zone.

Based on the individual metabolic thresholds, we will design five intensity zones. The zone of low-intensity training (LIT) corresponds to exercise carried out at an HR lower than that at LT1 (~ 20% of the HRR) and the zone of moderate intensity to exercise carried out between LT1 and the MLSS (~ 20–85% of HRR or between 1 and 2.3 Mmol/L), this in turn being divided into three equally-sized zones: low-moderate (M1), medium-moderate (M2) and high-moderate (M3) intensity. Finally, the zone of high-intensity training (HIT) (>MLSS, > ~ 85% of the HRR).

During the first month, participants will start carrying out sessions involving endurance exercise, which will be divided into 3 intervals of 8 min each at an M2 intensity, alternating with 2 min at an M1 intensity. In the session in which patients work independently, they will be monitored with HR monitor and it will be explained that they should exercise for 30 min and for as much of that time as possible at M1.

During the second month, the maximum intensity of the intervals will increase to M3, nearing the anaerobic threshold HR. Specifically, the fully supervised exercise will be divided into four intervals of 5 min at M3, alternating with 3 min at M1, while the indirectly monitored (semi-supervised) session will be of 30 min at M2 (Fig. 2).

**Fig. 2 Fig2:**
[figure not shown]
EfiKroniK exercise programme

Three months after the beginning of the project, the assessments are to be repeated and new intensity zones prescribed, in line with changes in functional capacity as assessed by the lactate tests. At this point, patients are to be given a report of the results of these assessments together with guidelines for exercising independently during the following months. During the same appointment, we will explain to patients how to use the HR zones prescribed during exercise and we will warn them about any potential risk factors detected [37–39]. Given that a relatively high proportion of people on the same training programme do not show a good response in various metabolic parameters [39, 40], patients who adapt well to the training will be recommended to continue exercising at a high-moderate intensity (M3), while those with a poorer response will be encouraged to continue their training at least at low- to medium-moderate intensities (M1-M2).

#### Strength and endurance exercises

Strength training is a key element of the exercise programme in these conditions which are associated with reduced peripheral muscle strength and a low level of fitness. The approach taken consists of exercising the largest muscle groups at high speed and moderate intensity with a moderate load. In each session, 5 exercises are performed involving major muscle groups, namely, the chest, quadriceps, back, hamstring and gluteal muscles, as well as the shoulder, these being performed in 2–3 series of 8–12 repetitions of 16–20 possible exercises (~ 55–65% of the 1 repetition maximum, seeking to avoid excessive muscle damage and inflammation) and using machines, dumbbells, weight bars and plates, elastic straps and wearable weights.

This type of strength training has shown to be effective for releasing anabolic myokines (IL-4, IL-13, IL-15, leukaemia inhibitory factor) and have great therapeutic potential against osteoporosis and sarcopenia/cachexia (responsible for around 20% of cancer-related deaths) associated with metastatic cancer and associated treatments [37, 40], as well as resulting in only mild muscle damage and inflammation.

